## Sample size calculation

Sample size calculation was carried out with the programme R Version 4.4.0, package ‘pwrss’ version 0.3.1. It is based on effect sizes of comparable interventions of the Mediterranean diet^(32)^ and mindful eating^(33)^ on the primary outcome of the study (BDI-II score). Using a conservative approach, we have used the lower effect size of d = 0·86 of the mindfulness intervention (Mediterranean diet: d = 1·7) to compute the required sample size. Considering a statistical power of *β* = 0·8 and *α* = 0·05, as well as a 20 % dropout rate for ANCOVA with main and interaction effects and baseline scores as covariate, *n* 64 subjects need to be recruited, that is, sixteen participants in each group.

For microbiome analysis, samples of *n* 32 healthy controls will additionally be analysed, representing the same number of participants receiving each intervention.

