### Secondary outcomes

#### Remission

Remission rates will be assessed as the number of patients who no longer show depressive symptoms, defined as BDI-II < 9.

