## Statistical analysis

The statistical analysis will be carried out using the programme R version 4.4.0. As a significance level, p ≤ 0·05 is defined. Data will be analysed as an intention-to-treat analysis. To handle missing data, the ‘missForest’ package in R will be used. This package implements a non-parametric imputation method based on random forests. This approach iteratively imputes missing values using a predictive model that leverages relationships among observed data while accounting for both continuous and categorical variables. Default settings for the algorithm will be used, which automatically selects the optimal number of trees and variables per split to maximise imputation accuracy. The primary outcome parameter is analysed confirmatory using a two-factorial ANCOVA, in which the main outcome parameter is modelled as a function of the two factors – mindful eating (yes/no) and Mediterranean diet (yes/no) – and the respective baseline values (linear covariates). Both main effects of the interventions and interactions are considered. Secondary outcomes will be exploratory (without correction for multiple testing) and analysed using the same models as the primary outcome. To estimate the clinical significance of the results, change scores and effect sizes (Hedges’ g) are calculated for between-group comparisons. The clinical relevance of the results is examined by comparing the number of participants who achieve a clinically relevant improvement of at least 5 points^(51)^ on the BDI-II between the groups at week 12 and week 24 using a logistic regression adjusted for the BDI-II baseline value (random effect). The same model is used to compare the number of patients between the groups who reach remission of depression at week 12 and week 24 (BDI-II < 9).

Mediator and moderator analyses are conducted with the PROCESS Package^(52)^. For the mediator analysis, the indirect effect of an independent variable on a dependent variable via a mediator and its significance are tested using the bootstrap method. Mediation paths can be identified and quantified with consideration of control variables. Concerning moderator analysis, the relationship between the moderator and the independent variable is analysed using product terms in the regression model. Strength and direction are determined using coefficients and statistical significance using the bootstrap method.

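### Remission in groups of 16 is analysed by plain logistic regression; if the befriending group has no remitter, which is plausible but not established, the group and interaction odds ratios have no finite estimate

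*Protocol article*

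**What the plan says.** The Remission section sets the endpoint: "Remission rates will be assessed as the number of patients who no longer show depressive symptoms, defined as BDI-II < 9". The Inclusion criteria section requires a BDI-II of at least 20 at entry.

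The Statistical analysis section first describes a logistic regression for the proportion improving by at least 5 points. It is adjusted for baseline BDI-II, which the text labels a random effect. The section then carries that model over: "The same model is used to compare the number of patients between the groups who reach remission of depression at week 12 and week 24". It names no penalised or exact method and no type of test. It does not say whether the groups are the four cells or the two factors. The same section makes secondary outcomes exploratory and gives them the primary outcome's models, in which main effects and interactions are both considered.

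On numbers, the Sample size calculation section says that 64 "subjects need to be recruited, that is, sixteen participants in each group". That figure rests on the continuous BDI-II score, using the "lower effect size of d = 0·86 of the mindfulness intervention". No remission rate is given for any group.

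**The concern.** A model that suits a 5-point improvement need not suit a fall of 12 points or more, and participants in the severe stratum (29 or more at entry) must fall by at least 21. Remission after befriending alone may be rare, and 16 participants is a small denominator.

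If no befriending participant remits, the data are separated. The likelihood keeps rising as the befriending log odds go to minus infinity, so every contrast with that cell, and the interaction, has no maximum-likelihood estimate. Software then prints an arbitrary large coefficient with a huge standard error and a Wald p-value near 1. This can happen when the interventions work and befriending does not. The label on the baseline covariate does not matter here, because the separation lies in the group terms.

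What is at stake is a usable effect estimate for the first-listed secondary outcome. Choosing a replacement after seeing an empty cell would also be a data-driven choice.

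**Working it through.** **The plan's own figure.** There is none for remission. The stated 64 is for the continuous score. A one-degree-of-freedom ANCOVA effect with f = 0.86/2 = 0.43, power 0.80 and α 0.05 needs 45 evaluable participants. That becomes 45/0.8 = 56.25, so 57, or 60 in equal groups. With 64 recruited and 20 % lost, 51 remain and power is 0.85. The stated figure is therefore not reproduced exactly but errs on the safe side, and it has no bearing on remission.

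**Inputs from the protocol.** Entry BDI-II ≥ 20; remission < 9, so the smallest qualifying fall is 20 − 8 = 12 points; 16 per group. The analysis is intention-to-treat with imputation, so 16 per group is the relevant denominator.

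**Assumptions, not in the documents.** Week-12 BDI-II is normal; the befriending mean m is 20 to 26 and the SD s is 8 to 12. Each intervention shifts the mean by 0.86 SD, additively.

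**Befriending remitters.** p = Φ((8.5 − m)/s); expected count = 16p; chance of an empty cell = (1 − p)^16.

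| m | s | p | expected of 16 | chance of none |
|---|---|---|---|---|
| 20 | 8 | 0.075 | 1.20 | 0.29 |
| 20 | 10 | 0.125 | 2.00 | 0.12 |
| 20 | 12 | 0.169 | 2.70 | 0.05 |
| 22 | 8 | 0.046 | 0.73 | 0.47 |
| 22 | 10 | 0.089 | 1.42 | 0.23 |
| 22 | 12 | 0.130 | 2.08 | 0.11 |
| 24 | 8 | 0.026 | 0.42 | 0.65 |
| 24 | 10 | 0.061 | 0.97 | 0.37 |
| 24 | 12 | 0.098 | 1.57 | 0.19 |
| 26 | 8 | 0.014 | 0.23 | 0.79 |
| 26 | 10 | 0.040 | 0.64 | 0.52 |
| 26 | 12 | 0.072 | 1.16 | 0.30 |

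The chance exceeds 50 % in 3 of the 12 scenarios. In general it does so only if p < 1 − 0.5^(1/16) = 0.042, that is, fewer than 0.7 expected remitters.

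**An example with an empty cell.** At m = 24, s = 10, a single intervention gives Φ(−1.55 + 0.86) = 0.245, or 3.9 of 16. The combination gives Φ(−1.55 + 1.72) = 0.567, or 9.1 of 16. Remitters of 0, 4, 4 and 8 of 16 (befriending, each single intervention, combination) are therefore a plausible table. Fitted without the baseline covariate:

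- Maximum likelihood, four groups: combination versus befriending log odds ratio 22.6, SE about 12,000, Wald p above 0.99. In factorial coding with interaction, the coefficients are about ±20 to 23 and every Wald p is above 0.99.
- Likelihood-ratio tests of the same models: four groups p = 0.003; combination versus befriending p = 0.0002; interaction p = 0.14.
- Main effects only: log odds ratio 1.58 for each factor, Wald p = 0.021.
- Fisher's exact test, 0/16 versus 8/16: p = 0.002.
- Firth, combination versus befriending. In this saturated table the fit equals adding 0.5 to each count, so the log odds ratio is ln(8.5/8.5) − ln(0.5/16.5) = 3.50. The penalised likelihood-ratio p is 0.0008.

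**The case against.** Four arguments weigh against the point.

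- **No projected count.** A reader might infer that the design itself projects almost no befriending remitters, or that an empty cell is likely. The documents do not support either. They give only a standardised effect on the continuous score, and the assumed grid runs from 5 to 79 %. At mean 24, SD 10, at least one remitter is the more probable result. This argument stands in full.
- **The test is not fixed.** A reader might also infer that a real benefit would be reported as no difference and that remission could say nothing about synergy. That holds only for Wald tests of cell or interaction coefficients. Likelihood-ratio tests of the same models, and a main-effects model, remain informative. Part of the gap between the Wald result and Firth's comes from the change of test. This stands for p-values. It does not rescue the estimates: wherever the empty cell has its own parameter, no maximum-likelihood fit yields a finite odds ratio. The main-effects model avoids that only by dropping the interaction, which the Objective section wants examined.
- **Low stakes.** Remission is exploratory, its counts would be visible, and depression benefit is also measured by the primary score, the 5-point response and the MADRS. This stands and sets the priority.
- **Left to an analysis plan.** Test type and fallback rules are usually written there, and their absence is no fault of an article. But the protocol does choose the model for remission, and that choice is what is questioned.

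**Conclusion.** The point holds as a modest one. The protocol applies to a demanding binary endpoint, in groups of 16, a model that gives no finite group or interaction odds ratio if one group has no remitter. Under an assumed befriending week-12 mean of 20 to 26 and SD of 8 to 12, the chance of that is 5 to 79 %, and 37 % at mean 24, SD 10. An empty cell is plausible, not established.

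The breakdown of the odds ratios under separation rests on no distributional assumption; how often it would occur rests entirely on the assumed means and SDs. The near-1 p-values need a Wald test as well, which the text neither states nor excludes. The primary ANCOVA is unaffected.

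**What to change.** In the Statistical analysis section, replace the sentence on remission with one that:

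- fits remission by Firth's penalised-likelihood logistic regression with Mediterranean diet, mindful eating, their interaction and baseline BDI-II as a numeric covariate, at week 12 and week 24;
- uses profile penalised-likelihood confidence intervals and tests in place of Wald ones;
- reports remitters as n/N per group, with a risk difference for each factor's margin (32 versus 32). In the example above that would be 12/32 − 4/32 = 25 percentage points for each factor.

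Use the same method for the 5-point response, so that the two binary analyses match.

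The cost is one sentence and a standard R package, with no new data or participants. The drawback is slight shrinkage of odds ratios towards 1 when events are plentiful.

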## Data management

Due to the nature of nutritional intervention, participants and providers cannot be blinded. Participants will learn about their group allocation at their first intervention appointment. Outcome measurements and data analysis will be conducted blinded. Questionnaires will be filled out digitally or on paper.

Study data are collected and managed using REDCap (Research Electronic Data Capture) electronic data capture tools hosted at meDIC/University Hospital Tuebingen^(53,54)^. REDCap is a secure, web-based software platform designed to support data capture for research studies. Data management will be in accordance with data safety guidelines, and data collection and storage will be performed in accordance with Good Clinical Practice Guidelines. There will be no data monitoring committee for the study because of the unblinded and monocentric design and because interventions are delivered only in the short term, and no harm is suspected.

## Dissemination policy

The study will be published in a peer-reviewed scientific journal. Results will also be shared with participants on request. Any changes in the protocol will be communicated to the ethics committee in the form of an amendment. Results will further be presented at conferences, and efforts will be made to make results accessible to a wide audience, not only in science but also in the general population.

## Discussion

The study has the potential to add valuable new data to the uprising field of the interplay of nutrition and mental health. The role of the Mediterranean diet in depression has already been studied^(17–19,55–57)^. These studies are conducted in Mediterranean and non-Mediterranean countries and address different target groups, as those with or without a diagnosis of depression, patients at high risk for CVD or young men. By including patients with co-morbid obesity, a new and vulnerable target group is studied^(6)^. Another novelty of the study is its factorial design, which allows separate evaluation of the effect of *what* food is eaten, in the manner of the Mediterranean diet, and *how* food is eaten, displayed as mindful eating.

Various secondary outcomes such as quality of life, self-efficacy and anthropometric measures will be assessed. They were chosen based on their potential role in the effect of the interventions. The choice of a valid control group in nutritional intervention trials is challenging^(58)^. The befriending control group was already successfully established in similar trials^(17,19)^ and allows for control of unspecific factors such as time, therapist relationship and expectations, which may play an important role in nutrition interventions and when studying mental health outcomes.

Changing eating behaviour is very complex. Many efforts are made to ease adherence. Food hampers, as well as many different supporting materials are provided. Further, the one-on-one setting allows focusing on the individual preferences and needs of participants.

If participants are interested, they will receive all printed materials of the other study groups on request after finishing participation. Adherence, dropouts and adverse events will be systematically analysed. In combination with the qualitative evaluation of the study, important findings regarding feasibility and implementation in a real-life setting will be gained.

The study evaluates the efficacy of the Mediterranean diet and mindful eating on depression severity and contributes to a better understanding of their mechanisms of action. By including participants with co-morbid depression and obesity, it serves a new and very important target group. The results may be seen as an important contribution to improving the supply situation for people suffering from obesity and depression.
